## **6.9 Sampling for Future Biomedical Research**

Blood, urine, and CSF samples, including residual samples already scheduled, will be collected for future research purposes to examine and/or research potential disease modifiers and/or biomarkers, including genetic parameters.

Patients are not required to participate in future biomedical research in order to participate in the study. Patients who agree to participate in this sampling will be required to provide an additional consent (contained in the main ICF).

## **6.10 Vital Signs**

Vital signs will be taken after a 5-minute seated rest and will include orthostatic blood pressure, pulse rate, respiratory rate, and oral or axillary body temperature. Vital sign measurements should be performed prior to any blood draws, whenever possible.

## **6.11 Electrocardiograms**

The 12-lead ECGs will be performed after a 10-minute supine rest and will include heart rate, QRS, and QT interval and will be read locally. The 12-lead ECGs should be performed prior to any blood draws, whenever possible. The Screening 12-lead ECG should be performed in triplicate.

## **6.12 Physical Examinations**

A full physical examination will be performed at Screening and Month 2. Brief symptom-based physical examinations will be performed at all other time points, unless a full physical examination is deemed necessary by the Investigator. New or worsened clinically significant abnormal findings will be recorded as AEs/SAEs

## **6.13 Height, Weight, Body Mass Index, and Waist Circumference**

Height will be measured at Screening only. Weight and waist circumference will be measured and BMI calculated during Screening, Month 2, and every 3 months post-administration of PR006A through Month 12. New or worsened clinically significant abnormal findings will be recorded as AEs/SAEs.

Waist circumference measurement should be made at the approximate midpoint between the lower margin of the last palpable rib and the top of the iliac crest. The tape should be snug around the body, but not pulled so tight that it is constricting. The mean of 2 measurements will be recorded.

#### **6.14 Neurological Examinations**

A full neurological examination will be performed at Screening and Month 2. Brief symptom-based neurological examinations will be performed at all other time points, unless a full neurological examination is deemed necessary by the Investigator. Symptom-driven evaluations may be performed at any time. New or worsened clinically significant abnormal findings will be recorded as AEs/SAEs.

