In the 6-month, multidose GLP NHP toxicology study (PRV-2018-028; n=6-7/dosing group), male and female cynomolgus monkeys 2 to 4 years of age were treated with PR006A administered once via ICM injection with a 7-day, 30-day, or 183-day post-administration

observation period. The study evaluated 2 dose levels: the highest dose ( $6.5 \times 10^{10}$  vg/g brain) was the maximum feasible dose achievable at the time of the experiment with 1.2 mL volume of undiluted test product, and the low dose ( $6.5 \times 10^9$  vg/g brain) is equivalent to one log lower than the high dose. The study also included a control arm in which animals received 1.2 mL of excipient only (20 mM Tris pH 8.0, 200 mM NaCl, 1 mM MgCl2, and 0.001% poloxamer 188). No adverse PR006A-related clinical observations, body weight changes, ophthalmic observations, or physical or neurological examination findings were noted. No in-life, clinical pathology, or anatomic pathology observations were observed that were considered related to PR006A.

No PR006A-related microscopic findings were observed in Day 7 or Day 30 animals. At the terminal sacrifice at Day 183, PR006A-related microscopic findings were observed in the dorsal funiculus of the cervical, thoracic, and (to a lesser extent) the lumbar spinal cord and the dorsal root ganglia (DRG).

Animals administered  $6.5 \times 10^9$  vg/g or  $6.5 \times 10^{10}$  vg/g had minimal axonal degeneration and, sometimes, minimal gliosis limited to the dorsal funiculus (white matter). Axonal degeneration was characterized by a few scattered nerve fibers ( $\leq 10$  per entire cross section) consisting of dilated axonal myelin sheaths that were either empty or containing cellular debris and/or phagocytic cells or spheroids (swollen eosinophilic axons). Gliosis was co-localized with axonal degeneration and was characterized by a few ( $\leq 10$ ) more fusiform nuclei (i.e., microglial cells) near affected axons. The limited extent of the degeneration in this study supported an interpretation that these changes were non-adverse.

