### 1.3 Risk/Benefit

This is a first-in-human study with PR006A, a first-in-class AAV9 vector-based gene therapy that transduces a functional copy of the human *GRN* gene. The population PR006A is intended for has FTD caused by the *GRN* mutation. FTD is a devastating neurological disorder in which there are no approved therapies. Available clinical and nonclinical data strongly support the role of PGRN reduction in pathogenic *GRN* mutation carriers as a causal factor in developing FTD, and that restoring PGRN levels will slow, halt, or possibly reverse the disease process. Such changes in disease pathology may translate into clinical benefit. However, there is no previous clinical data to indicate that increasing PGRN levels in the CNS will be beneficial, and it is not known whether increasing PGRN levels at the symptomatic stage of the disease will help prevent or slow downstream neurodegeneration.

In nonclinical efficacy and toxicology models, no PR006A-related adverse events (AEs) have been observed at the proposed starting dose. While minimal axonal degeneration and gliosis limited to the dorsal funiculus as well as minimally increased cellularity in small clusters occurred in the DRG of few PR006A-treated NHPs, these findings were non-inflammatory, limited in their extent, and without clinical correlate, and therefore were deemed non-adverse (PRV-2018-028). It is not predicted that the non-adverse findings in the NHPs will clinically translate to human patients. Notwithstanding, the protocol will exclude individuals with clinical evidence of peripheral symmetric sensory polyneuropathy and incidence of sensory symptoms will be monitored during the study using the Treatment-Induced Neuropathy Assessment Scale (TNAS).

PR006A immunogenicity in humans is currently unknown and will be studied as part of planned clinical studies. Overall, products (investigational and marketed) using the AAV9 vector have been safe and generally well tolerated in over 500 patients. Out of an estimated 21 clinical trials investigating AAV9-based gene therapies, 7 use an IT route of administration with approximately 60 patients having received an investigational therapy. In addition, all study participants will receive prophylactic corticosteroids and sirolimus to mitigate the risk of an immune response and will undergo longitudinal measurements for humoral and immune cellular responses. In the unlikely event of more pronounced immune

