### **6.18 Treatment-Induced Peripheral Neuropathy Assessment Scale**

The TNAS is a 9-item patient-reported outcome measure that rates symptom burden associated with treatment-induced peripheral neuropathy (TIPN). Patients are first asked to assess the severity of five common symptoms of TIPN as experienced in their extremities in the past 24 hours on an 11-point Likert scale ranging from “Not present” to “As bad as you can imagine”; symptoms assessed include numbness, tingling, pain, hot or burning sensations, and coldness. Patients are also asked to rate 4 items assessing the worst level of interference experienced in the last 24 hours caused by symptoms of TIPN: Difficulty using hands or fingers, trouble walking, trouble with balance or falling, and disturbed sleep; these 4 items are rated on an 11-point Likert scale ranging from “Have not interfered” to “Interfered completely.” ([Mendoza et al 2020](#)).

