| Urine biomarker                                                        | X                                                     | X  | X  | X  | X  | X  | X  | X                                           |
| Blood sample(s) for future biomedical research (optional) i | X                                                     | X  | X  | X  | X  | X  | X  | X                                           |

Abbreviations: AAV9, adeno-associated virus serotype 9; CDR plus NACC FTL, Clinical Dementia Rating staging instrument plus National Alzheimer's Coordinating Center frontotemporal lobar degeneration domains; CGI-I, Clinical Global Impressions-Improvement; CGI-S, Clinical Global Impressions-Severely; CSF, cerebrospinal fluid; C-SSRS, Columbia Suicide Severity Rating Scale; MINT, Multilingual Naming Test; MoCA, Montreal Cognitive Assessment; PGRN, progranulin protein; TMT-A, Trail Making Test Part A; TMT-B, Trail Making Test Part B; TNAS, Treatment-Induced Neuropathy Assessment Scale.

Note: Follow-up visits may be performed by telephone or video conference if the patient is not available to return to the clinic. Safety assessments may be obtained remotely for review by the Investigator.

- a. If a patient who received investigational product withdraws prematurely from the study for any reason, study site personnel should make every effort to complete the full panel of assessments scheduled for the end of treatment visit. Patients who withdraw during the treatment period will

complete the Month 12 (Year 1) assessments, while patients who withdraw during the follow-up period will complete the Month 60 assessments ([Section 4.2.2](#)). If the termination visit is more than 3 months prior to the scheduled Month 12 assessment, or more than 6 months prior to the Month 60 assessment for subjects who discontinue participation after Month 12, in addition to performing termination visit assessments, the investigator and study site personnel should make every effort to complete the Month 12 or Month 60 assessments, respectively, at the originally scheduled time points.

- b. Brief symptom-based neurological examinations will be performed, unless a full neurological examination is deemed necessary by the Investigator.

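### No full neurological examination is scheduled after Month 2, although the PR006A-related spinal cord and dorsal root ganglion changes in primates were seen only at Day 183

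*Protocol*

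**What the plan says.** Section 6.14 states: "A full neurological examination will be performed at Screening and Month 2. Brief symptom-based neurological examinations will be performed at all other time points". The sentence goes on to an exception, "unless a full neurological examination is deemed necessary by the Investigator", and the section adds: "Symptom-driven evaluations may be performed at any time". Table 13-1 footnote k repeats the rule for Year 1. For follow-up, Table 13-2 footnote b reads: "Brief symptom-based neurological examinations will be performed, unless a full neurological examination is deemed necessary by the Investigator". A note to Table 13-2 also lets follow-up visits take place by telephone or video when the patient cannot come to the clinic.

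On the nonclinical signal, Section 1.1.2 reports of the GLP primate study: "No PR006A-related microscopic findings were observed in Day 7 or Day 30 animals". At Day 183 it reports PR006A-related changes at two sites. Minimal axonal degeneration, sometimes with gliosis, was seen in the dorsal funiculus at both doses. Minimally increased cellularity was seen in the dorsal root ganglia of one low-dose and two high-dose animals.

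Section 1.3 responds by excluding patients with symmetric sensory polyneuropathy and by stating that "incidence of sensory symptoms will be monitored during the study using the Treatment-Induced Neuropathy Assessment Scale". Section 6.18 describes that instrument: "The TNAS is a 9-item patient-reported outcome measure". Section 7.1.1 lists both the TNAS and neurological examinations within the primary safety endpoint, measured up to 5 years.

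**The concern.** The protocol accepts that the primate finding deserves monitoring in patients. The most sensitive clinical tool it names, a full examination that can be compared with Screening, is scheduled once after dosing, at about Day 61. The primate changes were absent at Day 30 and documented at Day 183. From Month 3 on, the default examination is driven by symptoms, and the named scale is the patient's own report.

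The trial enrols patients with primary progressive aphasia and with CDR plus NACC FTLD sum-of-boxes scores of up to 15 on a scale ending at 24, in a progressive disease. Some of them may not report numbness or imbalance reliably, and fewer may do so as the years pass. A deficit that shows mainly as a sign, such as reduced vibration sense or a lost reflex, gives little reason to raise a complaint or to call for a discretionary full examination.

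At stake is the interpretation of one component of the 5-year primary safety endpoint. With 5 patients per cohort and a single, one-time dose, a report of no neuropathy should be separable from not having looked for it in a uniform way.

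**Working it through.** No power or sample-size figure is involved; the check is a count of visits and some calendar arithmetic.

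**Scheduled neurological examinations after dosing**
- Table 13-1: Months 1, 2, 3, 6 and 12, so 5.
- Table 13-2: Months 18, 24, 30, 36, 42, 48, 54 and 60, so 8.
- Total: 5 + 8 = 13. Full by schedule: 1 (Month 2). Brief by default: 12.
- After Month 2: 3 + 8 = 11, of which 0 are scheduled as full.
- The TNAS is scheduled at the same 13 visits.

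**Timing** (1 month = 365.25/12 = 30.44 days)
- Month 2: 2 × 30.44 = Day 60.9; with the +14-day window, up to Day 74.9.
- Gap to the primate observation: 183 − 60.9 = 122 days, or 183 − 74.9 = 108 days.
- Day 183 in months: 183/30.44 = 6.0. Carrying primate days over to patient days one for one is an assumption.
- Share of the study after Month 2: (60 − 2)/60 = 97%.

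**Dose context**
- The low primate dose was 6.5 × 10^9 vg/g brain (Section 1.1.2); the human starting dose is 2.7 × 10^10 vg/g (Section 1.2.5). Ratio: 0.65/2.7 = 0.24. The dorsal funiculus finding was therefore present at about a quarter of the starting dose, and the study tested no dose without it.

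**What the primate data can and cannot date**
- Necropsies were at Days 7, 30 and 183 only. Onset lies somewhere in that last interval of 153 days (183 − 30), and could fall before or after Month 2.
- There were 6 to 7 animals per dosing group. If that is the total over the three necropsy times, the average is 2.0 to 2.3 per group and time (6/3 to 7/3), so absence at Day 30 is itself weak evidence.

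**What is left after Month 2**
- TNAS: patient-reported. Section 6.18 gives the study partner no role in it.
- Eleven clinician examinations, symptom-based by default.
- Discretionary full examinations and symptom-driven evaluations, which will not be uniform across patients or cohorts.
- The study partner as informant (inclusion criterion 10) and the adverse-event question at each visit (Section 6.2.1.3).

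Most of these start from a symptom that someone notices and reports. The exception is a full examination that the Investigator chooses to do unprompted.

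**The case against.** The strongest counter-argument is that the primate evidence does not show that a full examination would find anything. The changes were microscopic and minimal, with at most 10 affected fibres per cross section. The same animals had no adverse PR006A-related neurological examination findings, and Sections 1.3 and 6.2.2.4 do not predict translation to patients. This stands. It limits the point to a modest improvement, but it does not remove it: non-translation is a prediction, and a first-in-human study is where it is tested.

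Several stronger readings are tempting, and the documents do not support them:
- A reader might infer that Month 2 is the only full examination possible. It is the only scheduled one; the Investigator may do others at any visit.
- A reader might infer that later sensory harm is left entirely to self-report. Eleven clinician examinations follow Month 2, a study partner is required, and Section 5.5.1.3 counts sensory symptoms found on examination as well as on the TNAS.
- A reader might infer that the lesion is expected in patients after Month 2. The protocol says the opposite, and onset in the animals is not dated within Day 30 to Day 183.
- A reader might take all patients to have impaired comprehension. Section 1.1 attributes that to the semantic variant of aphasia and says that carriers most commonly develop the behavioral variant. Entry scores run from 1 to 15, not only near 15.
- A reader might treat the 97% as a rate of missed events. It describes the calendar only.

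It is also fair that the content of a brief examination is undefined here and may be set out in study manuals that are not at hand. If those manuals require a fixed sensory and reflex check at every visit, much of the concern falls away; the protocol text does not require one.

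**Conclusion.** The point holds as a design weakness, not as a contradiction or a wrong figure. One of 13 scheduled post-dose neurological examinations is full, and none is scheduled as full after Month 2. That covers 58 of 60 months and includes Month 6, the visit closest to the only time at which the primate changes were seen. After Month 2, detecting a sensory deficit rests mainly on the TNAS, reported symptoms and Investigator discretion. Discretion does not close the gap, because a deficit without complaint rarely prompts its use.

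The consequence is for interpretation: a clean neuropathy result could reflect how it was measured as well as the safety of PR006A. No number of missed cases can be given. The conclusion assumes that primate time is a rough guide to human time, that brief examinations have no fixed sensory component, and that some enrolled patients cannot report sensory symptoms reliably. The change is worth making because it is cheap, with no claim that it would detect the primate lesion.

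**What to change.** In Section 6.14, Table 13-1 footnote k and Table 13-2 footnote b, specify that the neurological examinations already scheduled at Months 6 and 12, and yearly thereafter (Months 24, 36, 48 and 60) when the visit is in person, are full examinations with the same sensory and reflex components as at Screening. Add an eCRF field recording when a telephone or video visit prevented the examination, so that absence of findings can be told apart from absence of examination. On the TNAS, add a field noting when the patient could not answer reliably.

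The cost is a wording change in three places, two eCRF fields, and a longer examination at 2 + 4 = 6 existing visits per patient. No new visit is needed. Where follow-up is remote, the full examination will be missing, and the added field makes that visible.

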#### **6.15 Magnetic Resonance Imaging and Magnetic Resonance Angiography**

Brain MRA and brain MRI will be performed at Screening to evaluate eligibility and to determine whether the ICM procedure is safe for the patient. Screening MRIs will be read locally and centrally; MRAs will only be read locally. Post-baseline brain MRIs for safety evaluation will be performed without contrast unless specifically requested by the Investigator.

An MRI may be performed at any visit for safety monitoring if clinically indicated, as determined by the Investigator. After the 1-month safety MRI, follow-up MRIs may be done within a window of  $\pm 7$  days in order to give flexibility to patients and sites with scheduling. New or worsened clinically significant abnormal findings will be recorded as AEs/SAEs.

#### **6.16 Dual-Energy X-Ray Absorptiometry**

DEXA scans of the hip and spine will be performed at Screening and at Month 12 only in patients with known medical history of osteoporosis or osteopenia or with multiple risk factors (in addition to the planned exposure to the corticosteroid course) for osteoporosis. Abnormal Month 12 findings will be recorded as AEs/SAEs.

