#### **6.2.1.4 Reporting Adverse Events**

All AEs reported or observed during the study, as detailed in [Section 6.2.1.3](#), will be recorded on the AE page in the eCRF. Information to be collected may include but is not limited to the following:

- drug treatment
- dose
- event term
- time of onset
- Investigator-specified assessment of severity and relationship to investigational product
- time of resolution of the event
- seriousness
- any required treatment or evaluations
- outcome

Adverse events resulting from concurrent illnesses, reactions to concurrent illnesses, reactions to concurrent medications, or progression of disease states must also be reported. All AEs will be followed to adequate resolution. The Medical Dictionary for Regulatory Activities (MedDRA) will be used to code all AEs.

Any medical condition that is present at the time that the patient is screened but does not deteriorate should not be reported as an AE. However, if it deteriorates at any time during the study, it should be recorded as an AE.

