#### **6.2.2.2 Risks Associated with the Use of Immunosuppressants**

One loading dose of 6 mg oral sirolimus will be administered at Day -1, as well as a single dose of 1 g IV methylprednisone at Day 0. A concomitant maintenance dose of 2 mg/day sirolimus will be administered orally for 90 days starting at Day 0 which will then be tapered over the ensuing 15 to 30 days. The maintenance dose is administered to achieve trough sirolimus concentration of 4 ng/mL (range 2 to 8 ng/mL). One day after treatment with PR006A, patients will start prednisone 30 mg orally for 14 days, followed by a 7-day taper. At the Investigator's discretion, adjustments of dose and duration are permitted.

Corticosteroids are administered for prophylactic suppression of inflammatory responses and to improve viral transduction. Despite the beneficial effects of prednisone and sirolimus in the prevention and management of potential liver enzyme abnormalities, systemic immunosuppressants in this dose range can produce a variety of AEs ranging from mild irritability to life-threatening or even fatal biochemical effects including but not limited to impaired wound healing, interstitial lung disease, hyperglycemia, hypertension, lymphomas/malignancies, hyperlipidemia, decline in renal function, proteinuria, embryo-fetal toxicity, and male fertility. While patients will be excluded if they are at increased risk of AEs, if corticosteroid side effects emerge, corticosteroids will be stopped or tapered as medically indicated. Glucose level checks, HbA1c, fructosamine, blood pressure, body weight, cholesterol, urine protein, lipids, red blood cell counts, neutrophil counts, protein glucose, CSF cell counts, CSF protein levels, CSF glucose levels, sirolimus trough concentrations, BMI, waist circumference, and psychosis incidence/aggravation will be monitored at study visits occurring during corticosteroid usage and after prednisone

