discontinuation. The iDMC will assess safety variables as listed for the primary safety endpoints ([Section 2](#)) and as detailed in [Section 11.1.1](#). Patients must have evidence of a negative MTB test and pneumococcal pneumonia and shingles vaccination coverage (within 10 years prior to Screening; allowed during Screening Period but at least 4 weeks prior to sirolimus loading dose) in order to initiate prednisone or sirolimus. Additionally, if medically indicated and as per local standard of care, Principal Investigators may consider performing EBV, CMV, and JC virus testing as well anti-viral (e.g., valganciclovir) and/or antibacterial (e.g., low-dose Bactrim) prophylaxis during sirolimus course.

If steroid or sirolimus side effects emerge, these drugs will be stopped or tapered as medically indicated. Details regarding additional monitoring for corticosteroid and sirolimus-related events are provided in [Section 5.5.1.3](#)

If clinically indicated and/or as per local practice, concomitant gastroprotective prophylactic medication, as well as potassium and/or calcium/vitamin D3 and bisphosphonate supplementation, may be initiated. Specifically, for patients with pre-existing osteoporosis (without history of vertebral fracture in the past year) or history of fragility fracture, the Investigator should consider prescribing appropriate therapy intended to prevent/attenuate glucocorticoid-induced osteoporosis starting at the time of initiation of prednisone administration. The same consideration to provide therapy to prevent/attenuate glucocorticoid induced osteoporosis should be given to patients whose prednisone treatment may be extended beyond 6 weeks. A dual-energy x-ray absorptiometry (DEXA) scan will be performed at Screening and will be repeated at Month 12 for patients with baseline osteopenia or osteoporosis ([Section 6.16](#)). For patients receiving prednisone for more than 3 months, HbA1c will be measured at the end of prednisone therapy.

Continued participation in the study will not be affected if the patient or Investigator finds corticosteroid administration to be intolerable or the patient develops clinically significant AEs requiring early prednisone or sirolimus discontinuation.

The following TEAEs, which may be associated with immunosuppressant regimen (see above text), should be explicitly monitored:

- Peptic ulcer disease
- Erosive gastritis

- Osteoporosis
- Increase in body weight  $\geq 5\%$  from baseline

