### **7.1 Primary Endpoints**

#### **7.1.1 Primary Safety Endpoints**

The following primary safety endpoints are measured up to 5 years:

- Incidence and severity of TEAEs and SAEs, including clinically significant changes in vital signs, clinical laboratory assessments, C-SSRS, and TNAS; treatment-emergent transaminitis; treatment-emergent diabetes and prediabetes; treatment-emergent peptic ulcer disease and/or erosive gastritis; treatment-emergent osteoporosis; treatment-emergent increase in body weight  $\geq 5\%$  from baseline, treatment-emergent BMI  $>25$  or  $>30$ , and treatment-emergent increase in waist circumference  $\geq 15\%$  from baseline; incidence of Grade  $\geq 3$  infections; incidence/aggravation of psychosis; treatment-emergent hypercholesterolemia or hyperlipidemia; treatment-emergent interstitial lung disease; treatment-emergent opportunistic infections (including progressive multifocal leukoencephalopathy (PML) and BK virus-associated nephropathy); sirolimus trough levels; 12-lead ECGs; brain MRIs; physical examinations; and neurological examinations
- Sum of ARs and suspected ARs
- Sum of serious ARs and serious suspected ARs
- Incidence of procedure or treatment-emergent safety findings as per brain MRI.
- Change from baseline in immunogenicity of AAV9 and PGRN in blood at Day 14 and Months 1, 2, 3, 6, 9, and 12 and in CSF at Months 2 and 12.

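### Section 6.16 records every abnormal Month 12 DEXA scan as an AE even if unchanged, and weight, BMI and waist are declared measured to 5 years although scheduled measurement ends at Month 12

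*Protocol*

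**What the plan says.** Section 7.1.1 opens its list with "The following primary safety endpoints are measured up to 5 years". The list includes "treatment-emergent osteoporosis; treatment-emergent increase in body weight" of at least 5%, BMI above 25 or above 30, a waist increase of at least 15%, and treatment-emergent diabetes and prediabetes. The Synopsis and Section 2 carry the same time statement.

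Section 6.16 provides DEXA scans at Screening and Month 12 "only in patients with known medical history of osteoporosis or osteopenia or with multiple risk factors" for osteoporosis. Footnote p of Table 13-1 describes the same group. Section 6.16 then adds: "Abnormal Month 12 findings will be recorded as AEs/SAEs".

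Section 6.2.2.2 says that a DEXA "scan will be performed at Screening and will be repeated at Month 12 for patients with baseline osteopenia or osteoporosis".

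Section 6.2.1.4 says: "Any medical condition that is present at the time that the patient is screened but does not deteriorate should not be reported as an AE". Section 6.2.1.1 defines a treatment-emergent event as one absent before exposure, or one already present that worsens after it.

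Section 6.13 fixes the body measurements: "Weight and waist circumference will be measured and BMI calculated during Screening, Month 2, and every 3 months post-administration of PR006A through Month 12". Section 6.2.2.2 lists body weight and BMI among the monitored items and continues "waist circumference, and psychosis incidence/aggravation will be monitored at study visits occurring during corticosteroid usage", and also after prednisone is stopped.

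**The concern.** The primary safety endpoints are the list that the iDMC is told to assess (Sections 3.1.1 and 11.1.1), so the recording rules and time windows behind them should be exact. Three things are not.

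- The DEXA rule in Section 6.16 tells sites to enter AEs that Section 6.2.1.4 tells them not to enter. It does so in the patients most likely to have an abnormal scan already.
- Two sections give different groups for the Month 12 scan. The group affected, patients with risk factors but no bone disease at baseline, is one in which new osteoporosis could be detected.
- The stated 5-year measurement is not delivered by the schedule for several components, and the stated monitoring of weight and waist during corticosteroid use is not scheduled.

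A reader of the eventual report could take a bone event to be new when it is not, or take the absence of weight gain in years 2 to 5 as observed when nobody was scheduled to be weighed.

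**Working it through.** The protocol states no figure to reproduce here, so the check compares its sections with one another.

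**1. AE rule for DEXA.** Take a patient with known osteoporosis whose Screening and Month 12 scans are equally abnormal. Such a patient can be enrolled: exclusion criterion 3 names only osteoporosis with vertebral fractures in the year before Screening, and Section 6.2.2.2 makes provision for pre-existing osteoporosis.
- Section 6.16: abnormal at Month 12, so an AE or SAE.
- Section 6.2.1.4: present at Screening and not deteriorated, so not an AE.
- Section 6.2.1.1: neither absent before exposure nor worsened, so not treatment-emergent.
- Sections 6.12 to 6.15 (physical examination, body measurements, neurological examination, MRI): only new or worsened, clinically significant findings are recorded. Section 6.16 alone lacks this condition.

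Size of one misclassification in a full cohort: 1/5 = 20 percentage points.

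**2. Who has the Month 12 scan.** Take a patient with several risk factors and no osteopenia or osteoporosis at baseline.
- Section 6.16 and footnote p of Table 13-1: scanned at Screening and Month 12.
- Section 6.2.2.2: the Month 12 repeat is for baseline osteopenia or osteoporosis, so no repeat.

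**3. Stated window against schedule.** The stated window is 5 years, or 60 months. Table 13-2 has 8 follow-up visits (Months 18, 24, 30, 36, 42, 48, 54 and 60).
- Weight, BMI, waist: last scheduled at Month 12. Table 13-2 has no row for them, and vital signs as defined in Section 6.10 do not include weight. Months without a scheduled measurement: 60 − 12 = 48, and 48/60 = 80%. Follow-up visits with a measurement: 0 of 8.
- HbA1c: Table 13-1 schedules Screening, Day -1, Month 2 and Month 3, plus unscheduled visits. Section 6.2.2.2 adds one test at the end of prednisone if it lasts more than 3 months. By the regular schedule, 60 − 3 = 57 months have none. Glucose is in the standard chemistry panel (Section 6.5), and blood chemistry continues through Month 60.
- DEXA: one post-dose scan at Month 12, in the selected group, and none in the remaining 48 months.
- AE reporting continues to Month 60 for every patient.

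**4. Weight and waist during corticosteroid use.** Prednisone runs for 14 days from Day 1, then a 7-day taper, so the default course ends at 14 + 7 = Day 21. Table 13-1 has visits on Days 7, 14 and 21 and at Month 1, with no weight or waist measurement at any of them. The measurements on either side are Screening and Month 2.

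**The case against.** The strongest defence is that these wording gaps need not distort a reported result.

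- The endpoint is treatment-emergent osteoporosis. If Section 6.2.1.1 is applied at analysis, an unchanged scan drops out, because the Screening scan supplies the comparison. This stands as a limit on the consequence. It does not remove the conflict in what sites are told to record.
- A reader might infer that, with 2 of 5 patients having unchanged abnormal scans, a cohort would report 2/5 = 40% osteoporosis when the truth is zero. The documents do not support this: they give no share of patients with bone disease, and the treatment-emergent definition would exclude such scans if applied.
- A reader might infer that unscanned patients, or years 2 to 5, are counted as event-free. No text says so. Section 7.7.1 summarises the primary endpoints at time points where the variables are collected, and it names the Safety Analysis Set without giving a rule for patients who have no scan.
- The 5-year phrase may be an upper bound over a mixed list. The same list contains sirolimus troughs, scheduled only to Month 3, and immunogenicity, with named times ending at Month 12. That reading is plausible, but weight, BMI, waist, osteoporosis and diabetes carry no time of their own, so the text still claims more than the schedule provides.
- Diabetes and osteoporosis are not unobserved later, since glucose and AE reporting continue to Month 60. What is missing is systematic HbA1c and DEXA.
- The Month 2 weight does meet the second half of the Section 6.2.2.2 statement, monitoring after prednisone ends. A gain that persisted would be seen then, and unscheduled visits allow a weight. Only the during-use half is unmet.
- Section 6.2.2.2 could be read as a Screening scan for everyone, but it cross-refers to Section 6.16, so that reading is not secure. The firm disagreement concerns the Month 12 scan in patients with risk factors only.

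**Conclusion.** The point holds in a limited form. As written, Section 6.16 produces AE entries that Sections 6.2.1.1 and 6.2.1.4 do not support. Each one carried into an incidence moves it by 20 percentage points in a cohort of 5. How many would arise cannot be said, because the protocol gives no prevalence of bone disease in this population.

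Section 7.1.1 claims 5-year measurement for weight, BMI and waist, and the schedule delivers 12 of 60 months. For HbA1c the regular schedule delivers 3 of 60 months, softened by continuing glucose and AE reporting. Section 6.2.2.2 conflicts with Section 6.16 on the Month 12 scan, and with Table 13-1 on weight and waist during corticosteroid use.

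It does not follow that these endpoints cannot be measured, that reported incidences will be wrong by a known amount, or that DEXA is confined to patients with existing bone disease, since those with multiple risk factors are included.

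The study is small and wholly descriptive, which limits the damage. The AE recording rule and the visit schedule are nonetheless protocol content, and a statistical analysis plan cannot change what sites record or measure. The text should be corrected.

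**What to change.** - **Section 6.16:** record as AEs only Month 12 findings that are new or worsened relative to the Screening scan, in line with Sections 6.2.1.1 and 6.2.1.4.
- **Section 7.1.1, Section 2 and the Synopsis:** replace the single 5-year statement with the actual assessment window of each component.
- **Reporting of osteoporosis:** show the number of patients scanned beside any DEXA-based count. Keep worsening of existing disease and clinically diagnosed cases in the endpoint. Restricting it to patients with two scans and no osteoporosis at baseline would lose both.
- **Sections to reconcile:** Section 6.2.2.2 with Section 6.16 and footnote p of Table 13-1 on who has the Month 12 scan, and Section 6.2.2.2 with Table 13-1 on when weight and waist are measured. Which version is right is for the sponsor to settle.

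The recording-rule, window and reporting changes are wording only and cost little. The downside is that the stated windows become shorter.
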